### Subgroup analysis

Planned exploratory subgroup analyses will explore potential moderators of primary outcome treatment effect using key baseline factors: age, sex, ethnicity, and deprivation. This will indicate whether the QIC contributes towards reducing inequalities in care. Subgroup analyses are exploratory, providing estimates of the direction and size of any interactions.

### Secondary outcome analysis

For binary secondary outcomes (any insulin pump prescribing, sustained insulin pump prescribing), mixed effects logistic regression will be used, using the same approach as for the primary outcome.

For continuous secondary outcomes (glucose levels measured by HbA1c), we will use mixed effects linear regression and report estimated mean differences with 95% confidence intervals, *p* values and intra-cluster correlation coefficients.

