### Randomisation and blinding

Participating specialist teams will be randomised after agreement to participate and confirmation of eligibility. Specialist diabetes teams (clusters) will be independently randomised on a 1:1 basis to receive the intervention or waitlist only control (receiving the intervention after the trial follow-up period ends), using a computer-generated minimisation programme.

Minimisation factors: Baseline proportion moving onto a pump in the 15 months prior to the intervention period (above or below median); size of target patient population in specialist team (above or below median); previous QIC pilot participation [19] (yes or no).

Participating specialist teams will not be blinded to allocation.

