### Follow-up

We have chosen an 18-month follow-up period for two reasons. First, it reflects the duration of the QIC, plus 3 months to assess sustainment. Second, it allows for a period for teams engaging with the QIC to consider, plan and initiate changes in clinical practice.

All teams will be given the opportunity to receive the intervention alongside standard NDA feedback. It is not possible to support all teams at once. We will therefore randomly allocate half to receive the intervention, whilst the other half will receive the intervention 18 months later (control group) 3 months after intervention arm delivery is completed. Teams that choose not to be included in the evaluation will receive the intervention alongside the control group.

Allocation concealment is not feasible in this trial. We will maintain a log of those unblinded to allocation. This will include the intervention delivery team and those research team members who need to know allocations to undertake the study. The intervention supports teams to engage local patients to identify potential barriers and actions to improvement, as such patients may not be blinded to involvement in the intervention arm.

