### Primary and secondary outcomes

The primary outcome is the proportion of adults with type 1 diabetes and raised glucose levels (HbA1c above 69 mmol/mol) starting and continuing to use insulin pumps for at least 3 months within an 18-month follow-up period.

Our secondary outcomes are:Change in blood glucose levels as measured by HbA1c in people with type 1 diabetes and raised glucose levels between the latest measurement in the 12 months preceding the start of the intervention and the latest measurements recorded during the study period.Any record of insulin pump prescribing, including for periods shorter than 3 months.Insulin pump use sustained over at least 6 months.

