### Primary outcome analysis

The primary ITT analysis will compare the primary outcome between trial arms, using mixed effects logistic regression, with patients nested within specialist teams, and with specialist teams treated as a random intercept, adjusting for patient-level and team-level covariates (including patient age, sex, ethnicity, deprivation and team-level stratification factors). Estimated mean odds ratios will be reported with 95% confidence intervals, *p* values and intra-cluster correlation coefficients.

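### The HbA1c outcome is worded as a change score but modelled as a level, with no baseline HbA1c term named and no earliest date for the follow-up reading: a small, free gain in precision and clarity is available

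*Protocol article*

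**What the plan says.** All references are to the protocol article.

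- **Primary and secondary outcomes** defines the first secondary outcome as "Change in blood glucose levels as measured by HbA1c in people with type 1 diabetes and raised glucose levels", taken "between the latest measurement in the 12 months preceding the start of the intervention and the latest measurements recorded during the study period". No earliest date is set for the follow-up reading, and it is not tied to pump start.
- **Secondary outcome analysis** gives the model: "For continuous secondary outcomes (glucose levels measured by HbA1c), we will use mixed effects linear regression and report estimated mean differences". The quantity named is the level, not the change, and no covariates are listed. In the same section the binary outcomes are given more: "mixed effects logistic regression will be used, using the same approach as for the primary outcome". That clause is not attached to HbA1c.
- **Primary outcome analysis** describes its model as "adjusting for patient-level and team-level covariates (including patient age, sex, ethnicity, deprivation and team-level stratification factors". Baseline HbA1c is not named, but the list is introduced as a set of examples.
- **Patient eligibility** admits only people with HbA1c above 69 mmol/mol at baseline, so a baseline value exists for everyone.
- **Randomisation and blinding** lists three minimisation factors (prior pump uptake, size of the target population, pilot participation). HbA1c is not among them, and teams are not blinded.
- **Follow-up** justifies the 18 months partly by the time teams need to plan and start changing practice.
- **Data analysis** refers to a detailed pre-specified plan, which is not shown.

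**The concern.** Two things are loosely fixed.

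First, the outcome definition and the model do not describe the same quantity. A reader cannot tell whether the analysis is of change, of follow-up level alone, or of follow-up level adjusted for baseline. The three estimate the same randomised contrast with different precision. The third is never less precise in large samples, and its key covariate is already in the data.

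Second, the follow-up reading is the last one at any time after the start. For a patient measured only early, that reading precedes any pump start and any practice change that the 18-month period was chosen to allow for.

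Precision matters here because the contrast is averaged over the whole cohort, while only a minority is expected to start a pump. The economic evaluation also plans a cost per change in blood glucose, so a noisy or diluted HbA1c contrast would pass into that analysis.

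**Working it through.** The article gives no expected effect, SD, ICC or power for HbA1c, so there is no HbA1c figure to reproduce.

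**Inputs from the article:** 77 clusters, or 38.5 per arm; an average of 600 patients per team (the planning figure); an uptake difference of 10% − 2% = 8 percentage points (Study progress).

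**Assumed inputs:** pump effect on HbA1c 3 to 10 mmol/mol; SD 12 to 18, equal at baseline and follow-up; HbA1c ICC 0.01 to 0.05; correlation r between baseline and follow-up 0.4 to 0.7.

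**1. Whole-cohort difference implied by the uptake gap.** 0.08 × 3 = 0.24 and 0.08 × 10 = 0.80 mmol/mol.

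**2. Standard error of the baseline difference.** SD × √(2 × DE / (38.5 × 600)), with DE = 1 + 599 × ICC.
- SD 12, ICC 0.01: 12 × √(2 × 6.99 / 23,100) = 0.295.
- SD 18, ICC 0.05: 18 × √(2 × 30.95 / 23,100) = 0.932.

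**3. Change score against baseline adjustment, one r throughout.** The change-score SE multiplies step 2 by √(2(1 − r)); the adjusted SE multiplies it by √(1 − r²). Their ratio, adjusted to change, is √((1 + r)/2).

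| r | SE ratio | Cut in SE |
|---|---|---|
| 0.4 | √0.70 = 0.837 | 16% |
| 0.7 | √0.85 = 0.922 | 8% |

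The difference detectable with 80% power (two-sided 5%, so 2.80 × SE) runs from 0.64 to 2.86 mmol/mol for the change score and from 0.59 to 2.39 with adjustment.

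**4. If the level is analysed with no baseline at all**, which is the literal reading of the model sentence, adjustment cuts the SE by 1 − √(1 − r²): 8% at r = 0.4 and 29% at r = 0.7.

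**5. Allowing for clustering in the correlation.** The share of a team mean's variance that lies between teams is ICC / [ICC + (1 − ICC)/600]: 86% at ICC 0.01 and 97% at 0.05. What matters most is therefore how stable team means are. Suppose they correlate 0.9 over time (assumed), with r = 0.4 to 0.7 within teams. With w for the between-team share, the change-score variance is proportional to w × 2(0.1) + (1 − w) × 2(1 − r), and the adjusted variance to w × (1 − 0.81) + (1 − w)(1 − r²).
- ICC 0.01, r = 0.4: 0.342 against 0.282, an SE cut of 9%.
- ICC 0.05, r = 0.7: 0.212 against 0.200, an SE cut of 3%.

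The gain is then about 3% to 9%, and the change-score SE itself is only 0.15 to 0.45 mmol/mol.

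**6. Early readings.** If a fraction f of pump starters have a last reading that precedes any pump effect, the expected difference is (1 − f) times that in step 1.

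| f | Expected difference (mmol/mol) |
|---|---|
| 0 | 0.24 to 0.80 |
| 10% | 0.22 to 0.72 |
| 30% | 0.17 to 0.56 |
| 50% | 0.12 to 0.40 |

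The article gives no information on f.

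**The case against.** **The covariate point rests largely on silence.** The HbA1c sentence lists no covariates at all, the primary list is open-ended, and a detailed plan exists that is not shown. Modelling the level is compatible with baseline adjustment, which may already be intended. This stands: the article does not fix a model that excludes baseline HbA1c. What remains is that the outcome definition says change, the model says level, and neither names the covariate.

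**A reader might infer bias.** Everyone is selected for a high value, HbA1c is not a minimisation factor, and imbalance could enter a small contrast. The documents do not support that reading. Regression to the mean acts on both arms through the same entry rule. A change score is unbiased under randomisation, and chance imbalance has mean zero and is already in its SE. Only (1 − r) of an imbalance passes through: 0.3 to 0.6 mmol/mol per 1 mmol/mol at patient-level r of 0.7 to 0.4, but about 0.11 to 0.17 in the stable-team case of step 5 (1 − [0.9w + r(1 − w)]). An imbalance of 1 mmol/mol is also larger than one SE across the whole assumed range (0.30 to 0.93).

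**A reader might also infer that early readings overwhelm the effect.** They cannot; they shrink it in proportion. An early value counts only for a patient with no later reading in 18 months, and nothing in the article suggests that this is common. Bias would need measurement timing to differ by arm. That is conceivable, since teams are unblinded and the economic evaluation section foresees extra patient consultations, but it is not shown.

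**A late window has its own cost.** It drops patients without a late reading, and if clinic contact differed by arm, so would that selection. This stands, and it is why the window belongs in a sensitivity analysis.

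**Conclusion.** The point holds as a low-severity improvement to one secondary outcome. The definition and the model should describe the same quantity, and baseline HbA1c should be stated as a covariate. Against a change score, the gain in SE is about 8% to 16% for an assumed single correlation of 0.7 to 0.4, and about 3% to 9% if team means correlate 0.9 over time. Adjustment alone would not make the implied 0.24 to 0.80 mmol/mol difference detectable over most of the single-correlation range, since the detectable difference is still 0.59 to 2.39. That implied difference is itself an inference, as the article states no expected HbA1c effect.

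The open-ended follow-up reading is a rule the article does state, and it sits awkwardly with the reason given for an 18-month period. Its consequence is dilution, of a size that cannot be judged until measurement timing is known. Neither feature is shown to bias the comparison between arms.

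**What to change.** 1. Reconcile the outcome definition with the model: analyse the latest follow-up HbA1c value in the mixed linear model, with the patient's baseline HbA1c and the team mean baseline as covariates, alongside the covariates of the primary model. Including both baseline terms lets the within-team and between-team relationships differ, which step 5 shows is relevant.
2. Report by arm the time from the start of the intervention to the follow-up reading, and the number of patients with no follow-up reading.
3. Keep the any-time latest value as the main analysis, and add a sensitivity analysis restricted to late readings, for example months 12 to 18.

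The covariates cost nothing, since the data are already extracted. The timing table and the sensitivity analysis need only measurement dates and a few lines in the analysis plan. The restricted analysis loses patients without a late reading, so it should be read next to the timing table. If the plan that is not shown already contains the baseline adjustment, what remains is to align the wording and add items 2 and 3.

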### Missing data

Although we expect the level of missing data to be small, we will investigate patterns of missing data and reasons for missing data. We will compare the proportions of missing data between intervention and control groups.

We will build a multiple imputation model assuming data is missing at random for the primary outcome. A sensitivity analysis will consider a scenario where participants with missing outcome data are assumed not to move onto an insulin pump.

### Process evaluation

Our theory-informed, integrated process evaluation will comprise semi-structured interviews, surveys, documentary analysis and observations, with work package level analysis and synthesis.

Guided by the MRC Framework for developing and evaluating complex interventions, our objectives are to:Describe how implementers engage with the QIC intervention overall to support improvement activity and how context influences this work (implementation and engagement).Assess fidelity of delivery, receipt and enactment of the QIC intervention (fidelity).Describe how teams enact tailoring (tailoring).

### Theoretical approach

The evaluation will draw upon the same theories applied in developing the QIC intervention: Organisational readiness to change theory [17] to describe the target behaviours undertaken by intervention recipients; Normalisation Process Theory (NPT) [25] to explore implementation, and Behaviour Change Techniques (BCTs) [22] to describe delivery (Fig. 2).

The process evaluation will investigate whether hypothesised mechanisms for achieving change in both professional behaviour (what intervention recipients do) and patient-level outcomes (the use of insulin pumps) are evident when the QIC is used in practice, and what wider (and perhaps unanticipated) factors affect these mechanism-outcome relationships.

The logic model outlines the BCTs intended to trigger NPT mechanisms within the QIC intervention and targeted behaviours of specialist diabetes teams. We will draw on this logic model and the fidelity assessment approach of Lorencatto et al. [26] to assess the extent to which intervention components are delivered by intervention facilitators and received by specialist diabetes teams and if targeted behaviours are enacted as intended.

The QIC supports teams to explore influences upon performance, identified using the Theoretical Domains Framework (TDF) [27] and to select improvement actions aligned to these influences. Previously identified influences upon insulin pump use include patient factors (e.g. knowledge and skills), staff factors (motivation; beliefs about acceptability to, and consequences for, patients; beliefs about capacity and capability) and contextual factors (e.g. culture, funding, time). The tailoring evaluation will describe the selected improvement actions using the Expert Recommendations for Implementing Change (ERIC) [28] compilation of implementation strategies, and the template for intervention description and replication (TIDieR) framework. The analysis will be ongoing and iterative and draw upon other approaches from implementation science where relevant.

### Participants

We will include both specialist diabetes teams (typically including diabetologists and nurses) taking part in the study, and staff delivering the QIC intervention.

### Sampling and recruitment

We will sample participants from both intervention and control arms, weighted towards the former and aiming to ensure diversity of teams, service settings and patient population characteristics.

To limit participant burden, we will sample from around half (30) of the intervention teams for interviews, but from all intervention teams for observations and documentary analysis. Documents will include those produced within QIC workshops (for which we will give authors the opportunity to have their data excluded from the analysis) and organisational documents (e.g. local reports with appropriate permissions).

For interviews, we will undertake strategic sampling within the intervention arm, for example, by baseline proportion moving onto a pump in the 15 months prior to the intervention period (above or below median) and number of patients served by the specialist team (above or below median). We will sample from 8 to 12 control arm teams.

### Data collection

We will collect data from both intervention and control (teams assigned to later receipt) arms to explore ‘implementation as usual’ work for the NDA and any potential contamination between study arms. We will use four qualitative methods: around 60–80 theory-informed, semi-structured interviews, 4–8 surveys, analysis of up to around 120 documents and an estimated 55 h or less of observations. Where appropriate, the data will be used for all three process evaluation objectives (process and engagement, fidelity, tailoring) and the WP3 economic evaluation.

We will interview diabetes team members at multiple time points. The interviews will use a topic guide developed from our aforementioned theoretical approaches, including open questions for exploring barriers, facilitators and mechanisms related to NPT and BCTs. Interviews will also include more tailored questioning, developed from prior analysis of other data sources (documents and observation), and serving as prompts for more detailed investigation. An initial round of approximately 20 interviews will include both intervention deliverers and intervention arm participants early during intervention delivery to assess intervention engagement, fidelity, and tailoring. A further 40–50 interviews towards the end of the intervention period will seek more reflective data on intervention engagement and perceptions (including tailoring) and data required to complete fidelity assessment. This latter set of interviews will include 8–12 interviews with control arm participants to focus on team experiences of undertaking quality improvement in relation to the NDA in the absence of intervention, thus providing contextual data about ‘implementation as usual’. Combined with data from intervention participants, this will also provide scope to explore and understand any contamination across trial arms (e.g. if control participants mention access to QIC intervention documentation).

We will collect up to 55 h of observational data with intervention participants only, contributing data on implementation, engagement, fidelity and tailoring. This will capture participant descriptions of both planned and completed improvement actions. The observations will include recorded virtual interactive educational workshops, virtual outreach sessions and multisite facilitated meetings. Around two thirds of these data will be captured within the first 3 months of intervention delivery, allowing later interviews to focus more directly on issues arising from the observations. We will record intervention exercises and monthly virtual facilitated meetings for subsequent structured observational analysis. We will conduct more focused qualitative observations at some sites (identified at interview), to include meetings of implementation teams and meetings with key stakeholders (either in real time or recordings), as available and appropriate.

Around 120 documents for analysis will include materials concerning intervention exercises and activities, including stakeholder maps, logic models, action plans, and summaries of any discussions and meetings available to the research team. We anticipate the majority of these will concern intervention arm participants and provide additional detail for assessing fidelity of delivery, receipt and enactment and understanding tailoring activity. We will seek some documentation for analysis from control arm participants towards the end of the intervention period. These documents will be identified during control participant interviews and requested for inclusion in the study if available. They will likely comprise internal quality assurance reports and will help understand ‘implementation as usual’.

We will use an online survey to collect data from those intervention deliverers who provide brief input into intervention delivery. The survey will be emailed within the first 3 months of intervention delivery.

### Data analysis

Iterative analysis of interview data will use both inductive and deductive approaches, according to standard procedures [29, 30]. For example, the fidelity assessment will deductively seek the presence or absence of the enactment of target behaviours; the evaluation of implementation will inductively explore influences on engagement. Documents will be read in parallel by two researchers who will extract data for analysis according to the different process evaluation objectives. For implementation and engagement, these documents will be used to develop prompts and more detailed questions within the topic guide when interviewing the team members who authored them. For investigation of tailoring processes, documents will prompt questioning about the influences teams identified and how (and why) they linked these to their documented strategies. For fidelity, documentary analysis will focus on enactment of target intervention behaviours (e.g. use of the TDF to identify influences; the development of a list of stakeholders for engagement). We will take a more structured approach for observational data, assessing fidelity through coding and comparing the BCTs in the manual with those observed in delivery. In total, 36 h of the delivered intervention sessions will be coded (12 h of virtual interactive educational workshops, 12 one-to-one virtual outreach sessions and 12 multisite virtual facilitated meetings). These will be distributed across the delivery period, in accordance with the National Institutes for Health Behaviour Change Consortium recommendations. Eighty to 100% adherence to intervention specifications represents ‘high’ fidelity of delivery, 51 to 79% represents ‘moderate’ fidelity, and < 50% or less represents ‘low’ fidelity [31].

Our multi-stage analysis will occur concurrently with data collection to allow for emerging trends found in earlier fieldwork to be explored later. We will share interim analyses with stakeholders to identify additional avenues for exploration in later interviews and documentary analysis. This wider group will include clinicians, people with diabetes, policy leads and implementation scientists.

We will undertake workshops for integrative analysis of the different data sources (from interviews, observations and document analysis) to address the three investigative objectives of the process evaluation: implementation and engagement; fidelity and tailoring (1–2 half-day workshops per investigation). The analysis workshops will explicitly reconnect and explore the data and findings to develop higher level analyses with reference to NPT, organisational readiness and BCTs, and the matching of improvement strategies to barriers and facilitators using causal models [32]. Project team and stakeholders will be invited to these workshops as appropriate.

